## Abstract

**Background:**

Black adults in the United States experience disproportionately high rates of tobacco- and obesity-related diseases, driven in part by disparities in smoking cessation and physical activity. Smartphone-based interventions with financial incentives offer a scalable solution to address these health disparities.

**Objective:**

This study aims to assess the feasibility and preliminary efficacy of a mobile health intervention that provides financial incentives for smoking cessation and physical activity among Black adults.

**Methods:**

A total of 60 Black adults who smoke (≥5 cigarettes/d) and are insufficiently physically active (engaging in <150 min of weekly moderate-intensity physical activity) will be randomly assigned to either HealthyCells intervention (incentives for smoking abstinence only) or HealthyCells+ intervention (incentives for both smoking abstinence and daily step counts). Participants will use study-provided smartphones, smartwatches, and carbon monoxide monitors for 9 weeks (1 wk prequit date through 8 wk postquit date). Feasibility will be evaluated based on recruitment rates, retention, and engagement. The primary outcomes include carbon monoxide–verified, 7-day smoking abstinence at 8 weeks postquit date and changes in average daily step count. Feasibility benchmarks include a recruitment rate of ≥5 participants per month, a retention rate of ≥75%, and a smoking abstinence rate of ≥20% at 8 weeks postquit date. Expected increases in physical activity include a net gain of 500 to 1500 steps per day compared to baseline.

**Results:**

Recruitment is expected to begin in February 2025 and conclude by September 2025, with data analysis completed by October 2025.

**Conclusions:**

This study will evaluate the feasibility of a culturally tailored mobile health intervention combining financial incentives for smoking cessation and physical activity promotion. Findings will inform the design of larger-scale trials to address health disparities through scalable, technology-based approaches.

**Trial Registration:**

ClinicalTrials.gov NCT05188287; https://clinicaltrials.gov/ct2/show/NCT05188287

**International Registered Report Identifier (IRRID):**

PRR1-10.2196/69771

## Introduction

### Background

In the United States, tobacco- and obesity-related diseases are among the top 10 leading causes of death in the Black and African American (henceforth Black) population, and these diseases are more common and deadlier among Black adults compared with the overall US population [1-3]. For example, while smoking prevalence is similar among Black and White adults, Black adults are less likely to quit smoking than other racial and ethnic groups [4-6], and rates of lung cancer incidence and mortality are higher among Black male individuals than White male individuals [3]. Likewise, the Black population has high rates of obesity in the United States [7]. Physical inactivity (ie, no physical activity outside of work during the past month), a leading cause of obesity [8,9], is higher among Black adults compared with most other racial groups [8,9]. High rates of smoking (14.2%) [10] and insufficient physical activity (30%) [11] among Black adults are important modifiable health risk factors for cancer and chronic illness [12]. Interventions that simultaneously address these behaviors may promote holistic lifestyle changes, provide significant health benefits, and increase health equity within the Black population [13,14].

Multiple health behavior change (MHBC) interventions are defined as those that promote 2 or more health behaviors and thus have a more comprehensive focus on lifestyle health promotion [15,16]. Smoking and low physical activity are strong candidates for these interventions because people who smoke generally report less physical activity than those who do not smoke [17], and individuals may benefit from replacing smoking with physical activity during a quit attempt [18]. Importantly, engaging in physical activity may increase self-efficacy for quitting and alleviate cigarette cravings during withdrawal [19-22]. Physical activity also improves mood and reduces stress, which are common triggers for smoking relapse [23]. However, numerous studies have shown mixed results regarding the physical activity’s effectiveness for smoking cessation [24], in part because adherence to physical activity varies significantly across individuals [23,25,26], with stronger adherence among adults with existing physical activity habits and strong social support, and the type of activity (eg, low-intensity activity vs high-intensity activity) [27].

Low-intensity activities, such as walking, may be more practical and palatable for people trying to quit smoking while still offering benefits for smoking cessation, such as reduced cravings and stress relief [13,19,28]. Low-intensity activities may also promote greater adherence to physical activity because they are accessible, comfortable, and less likely to cause fatigue or injury than high-intensity workouts [29]. Furthermore, low-intensity activities can be included in daily routines, such as walking to a bus stop or church [30]. The inclusivity and ease of low-intensity physical activity may encourage long-term engagement and consistency. Thus, combining low-intensity physical activity with other cessation strategies may synergistically increase the likelihood of smoking cessation and have a greater impact on overall health.

Contingency management (CM) is a simple, powerful, and widely used behavioral strategy where tangible rewards are offered for meeting a prespecified behavior change goal [31-33]. CM is efficacious for improving smoking cessation and physical activity [34-38], but common concerns about CM are intervention costs and maintenance of long-term behavior change once incentives cease [39]. Yet, recent research on smoking and physical activity has shown that CM interventions are cost-effective, and even small financial incentives can lead to long-term changes in smoking and physical activity after incentives are withdrawn [34-38]. Thus, an MHBC intervention that incentivizes behavior change could help Black adults initiate and sustain smoking cessation and adequate physical activity in conjunction with other recommended tobacco treatment components (ie, counseling and pharmacotherapy) [40].

Despite the rapid growth of mobile health (mHealth) technologies, such as smartphone apps, that offer new opportunities to reach and treat at-risk populations, Black adults remain underrepresented in mHealth research [41]. As of 2024, 84% of the Black population owned a smartphone [42]; therefore, app-based interventions have the potential to increase the reach and use of effective treatments for smoking and physical activity within this population. Furthermore, apps combined with sensors and wearables can be powerful tools for self-regulation [42], which is a core component of behavior change [43], and can provide frequent feedback and engagement opportunities. Initial evidence suggests that app-based interventions may be a useful supplement to more intensive behavioral or pharmacological treatments and may even show comparable outcomes to traditional face-to-face interventions in some cases [44-47]. Furthermore, smartphone apps can be used to characterize the behaviors, needs, and outcomes of traditionally understudied and underserved groups.

Research indicates that interventions incorporating culturally relevant content resonate with Black adults, enhancing their motivation and commitment to behavior change [48-53]. Such content has increasingly been incorporated into mHealth interventions targeting smoking cessation and physical activity among Black adults [54-57]. Drawing from publicly available resources such as *Pathways to Freedom—*a short documentary highlighting the historical and cultural ties between the Black community and tobacco use and incorporating health education and culturally relevant messages to motivate Black adults to quit smoking [48,49]—mHealth apps can provide educational content on the historical and social influences of smoking within the Black community. mHealth apps can also provide motivational messages and stress-management techniques grounded in culturally relevant themes, such as prayer and seeking support from family and friends. Furthermore, app-based interventions can deliver education about the purpose and benefits of nicotine replacement therapy (NRT) and debunk myths and misconceptions about NRT that are present in this population [58-60]. Apps can also make it easier for Black adults to create activity goals that reflect their current life circumstances and environment [61,62], and these goals can be adjusted dynamically based on daily performance and feedback, ensuring that goals remain challenging yet attainable. This content can be presented alongside success stories from notable and relatable Black figures to provide additional motivational support [63-65]. Altogether, when delivered with evidence-based treatment for smoking cessation and physical activity, culturally relevant content may reinforce the quit journey and help address common challenges that Black adults face when quitting smoking and engaging in physical activity.

### Objectives

The purpose of this project is to explore the feasibility of an app-based MHBC intervention (HealthyCells) for Black adults who smoke and are insufficiently physically active. In addition to evidence-based tobacco cessation treatment [66], HealthyCells will incentivize daily smoking abstinence, while an enhanced version of the intervention, HealthyCells+, will also include incentives for meeting physical activity goals [36,67]. The inclusion of 2 active study conditions allows for a direct comparison to evaluate the added benefit of financial incentives for physical activity. The central hypothesis is that participants in the HealthyCells+ group will demonstrate greater increases in daily physical activity (measured via step counts) and improved smoking abstinence rates compared to those receiving smoking cessation incentives alone (HealthyCells). HealthyCells will also include an interactive educational e-book experience inspired by the documentary *Pathways to Freedom* [48,49], designed to guide individuals during their quit attempt and provide opportunities to set personalized activity goals, which can be dynamically adjusted daily to reflect current readiness. The primary aim will be to demonstrate intervention feasibility, including recruitment, retention, and adherence metrics, along with rates of carbon monoxide (CO)–verified smoking abstinence and prequit and postquit changes in physical activity.

## Methods

### Overview

Black adults who smoke and are insufficiently physically active (ie, not meeting physical activity guidelines) [68] will be randomly assigned to 1 of the 2 versions of an MHBC intervention that targets smoking cessation and insufficient physical activity: (1) HealthyCells (incentives for smoking abstinence only) or (2) HealthyCells+ (incentives for both smoking abstinence and physical activity). Both groups will receive a comprehensive tobacco treatment intervention, including 8 weeks of NRT, an initial counseling session to create a quit plan, and 5 weekly counseling sessions (6 sessions in total). Likewise, all participants will receive a study-provided smartphone and intervention app, a Samsung smartwatch to measure daily steps, and a Bedfont iCOquit Smokerlyzer to verify smoking status. Participants will be asked to use their assigned app and equipment for 9 weeks (1 wk prequit date through the eighth wk postquit date).

### Ethical Considerations

This study was approved by the institutional review board of the University of Oklahoma Health Sciences Center (protocol #14094), and the study was registered at ClinicalTrials.gov (NCT05188287). All procedures involving human participants will adhere to the Declaration of Helsinki and relevant institutional guidelines. Written informed consent will be obtained digitally from all participants before enrollment, and they will be informed of their right to withdraw from the study at any time without penalty. To ensure privacy and confidentiality, participant data will be deidentified and stored on a secure, password-protected server. All breath sample photos and step count uploads will be encrypted, with access restricted to authorized research personnel. Following a structured and transparent payment schedule, participants will receive compensation based on their engagement with study activities, including breath sample submissions, step count verifications, surveys, and interviews (refer to the Study Compensation section). To protect participant privacy, all devices used for data collection, including Samsung smartphones and smartwatches, will be reset to factory settings after study participation has ended for each participant. Any adverse events or deviations from the protocol will be promptly reported to the institutional review board in compliance with ethical oversight requirements.

### Theoretical Framework

As shown in Figure 1, this intervention will be guided by self-determination theory principles [69-72]. Self-determination theory posits that two forms of motivation are involved in behavior change: (1) autonomous motivation and (2) controlled motivation [72]. Autonomous motivation consists of engaging in behavior out of curiosity, interest, a sense of challenge, or for its inherent enjoyment. Conversely, controlled motivation involves engaging in a behavior because of external rewards or punishment avoidance [72]. Autonomous motivation is associated with sustained behavior change, whereas controlled motivation is related to temporary change [73]. CM interventions provide financial rewards for immediate behavior change, primarily targeting controlled motivation [74].

**Figure 1 figure1:**
[figure not shown]
The theoretical framework of HealthyCells app, a multiple health behavior change intervention for smoking cessation and physical activity.

Incentives can be paired with resources and activities that cultivate autonomous motivation to sustain long-term behavior change [75]. The research team created an interactive educational e-book experience inspired by *Pathways to Freedom* [48,49] intervention that focuses on several key topics highlighted in Textbox 1, such as the harms of smoking, tobacco marketing, NRT education, and stress management, and includes narratives from several prominent Black individuals who have struggled with smoking, such as the former US President Barack Obama [76]. The research team also developed a personalized activity goal algorithm based on findings from mHealth physical activity interventions [54,77] and qualitative interviews with Black adults [61,78].

Overview of topics covered in the HealthyCells, Healthy Habit e-book.
**Chapters and interactive educational content**
Chapter 1: discusses health and economic harms caused by smoking and the benefits after quittingChapter 2: covers the hidden history of Black adults and the tobacco industryChapter 3: describes how habits are created and why smoking is one of the deadliest habits to breakChapter 4: provides an overview of how nicotine reinforces the smoking habitChapter 5: reviews the purpose and benefits of nicotine replacement therapy

### Inclusion and Exclusion Criteria

Inclusion criteria for the participants will be as follows: (1) resident of Oklahoma (verified via driver’s license or ID); (2) aged ≥18 years; (3) self-identify as *Black* or *African American*, either alone or in combination with other races or Hispanic ethnicity; (4) smoke ≥5 cigarettes or cigarette equivalents per day (ie, cigars and cigarillos); (5) currently (per self-report) engage in <150 minutes of moderate-intensity aerobic physical activity or <75 minutes of vigorous-intensity aerobic physical activity per week [68]; (6) willing to use NRT, a smartwatch, or the study app and able to attend smoking cessation counseling; (7) willing to quit smoking within the next 3 weeks; and (8) exhaled CO level of >6 ppm at app activation.

Exclusion criteria for the participants will be as follows: (1) unwilling to complete the screening survey, (2) unable to understand or speak English, (3) not a US citizen or permanent resident (due to university taxation policies), (4) unwilling to provide social security number, US residency status, or university employee status (to adhere to university reporting requirements), (5) unwilling to abstain from smoking marijuana or cannabis during their quit attempt, (6) unwilling to provide a picture of a tobacco product (to provide initial evidence of current smoking), (7) medical condition (per self-report) that is a potential contraindication for NRT use (eg, uncontrolled hypertension, heart disease, or recent heart attack), or (8) has had a severe allergic reaction or side effect from the use of NRT.

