### Postintervention Assessment and Treatment Outcomes

At the eighth week postquit date, participants will complete a postintervention assessment via REDCap [85], answering questions similar to those in the baseline assessment to track changes in physical and mental health and health behaviors and to assess app impressions (Multimedia Appendix 1). A final semistructured interview will gather feedback on the app and suggestions for improvement (Table 1). The primary outcome for smoking cessation will be CO-verified, 7-day point prevalence smoking abstinence at 8 weeks postquit date, which will be assessed via smartphone-based self-report and a corroborating CO assessment. Expired CO is a valid indicator of smoking and cessation and compares favorably with cotinine and other biochemical measures [101]. Daily abstinence will be examined as a secondary outcome and defined as self-reported abstinence within the day combined with 2 breath CO sample submissions <6 ppm and identity verification. The number of days and consecutive days of CO-verified abstinence will be explored as additional outcomes. The other primary outcome will be the net change in average daily steps during the eighth week postquit date compared with average daily steps the week before the quit attempt (HealthyCells+ group only). Second, we will explore the number of total and consecutive days that ≥6000 steps were achieved as additional outcomes [102]. A valid day of observation for daily steps will be defined as (1) a smartwatch that was worn for at least 10 waking hours with (2) ≥500 steps taken within a day [103].

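### Inclusion criteria 5 and 6 are joined by 'or', so as written they admit people already active at one intensity and people unwilling to wear the watch

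*Protocol article*

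**What the plan says.** Three places in the protocol article define who is insufficiently active.

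- **Inclusion and Exclusion Criteria, criterion 5:** people who "currently (per self-report) engage in <150 minutes of moderate-intensity aerobic physical activity or <75 minutes of vigorous-intensity aerobic physical activity per week".
- **Abstract, Methods:** people who are "insufficiently physically active (engaging in <150 min of weekly moderate-intensity physical activity"), with no mention of vigorous activity.
- **Methods, Overview:** "Black adults who smoke and are insufficiently physically active (ie, not meeting physical activity guidelines"), citing the same guideline as criterion 5.

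Criterion 6 requires people to be "willing to use NRT, a smartwatch, or the study app and able to attend smoking cessation counseling". The Overview then expects everyone to use everything supplied: "Participants will be asked to use their assigned app and equipment for 9 weeks". Under Postintervention Assessment and Treatment Outcomes, "The other primary outcome will be the net change in average daily steps during the eighth week postquit date" compared with the week before quitting. A day counts there only with at least 10 waking hours of watch wear and at least 500 steps. The Analytic Plan requires at least 4 valid days for a participant to enter the step analysis.

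**The concern.** The two limits in criterion 5 look like two alternative ways of meeting a guideline. If either amount is enough, failing to meet the guideline means being below both. Joining the two limits with 'or' reverses this, because being below either one is then enough to enter.

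Criterion 6 has a similar fault. The step outcome cannot be observed without the watch, yet willingness to wear it is only one of three options.

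If the rules were applied as written, the enrolled group would be wider than the population the trial names. The recruitment rate and the 500 to 1500 step benchmark would then describe that wider group, and some participants could supply no step data. Eligibility is also hard to repair later, since removing randomized people from a sample of 60 would be a post hoc exclusion.

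**Working it through.** The article gives no figure to reproduce. The check applies each stated rule to example people.

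**Criterion 5.** Let M and V be weekly minutes of moderate and vigorous activity. The rules compared are:

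- criterion 5 as written: M < 150 or V < 75
- abstract: M < 150
- below both limits: M < 150 and V < 75
- combined total: M + 2V < 150. The weight of 2 is an assumption taken from the ratio of the two limits, 150/75 = 2.

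| M | V | As written | Abstract | Below both | Combined total |
|---|---|---|---|---|---|
| 0 | 0 | in | in | in | 0, in |
| 100 | 50 | in | in | in | 200, out |
| 149 | 74 | in | in | in | 297, out |
| 300 | 0 | **in** | out | out | 300, out |
| 0 | 100 | **in** | **in** | out | 200, out |
| 150 | 75 | out | out | out | 300, out |
| 200 | 100 | out | out | out | 400, out |

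Three results follow.

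1. As written, the criterion turns away only people with M ≥ 150 and V ≥ 75 together.
2. The person with 300 and 0 is eligible under criterion 5 and not insufficiently active under the abstract. This contradiction needs no outside source. The conflict with the Overview rests on the assumption that either amount alone meets the guideline.
3. The abstract cannot simply replace criterion 5. It admits the person with 0 and 100, whom the Overview would exclude under the same assumption.

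**Criterion 6.** There are 2 × 2 × 2 = 8 combinations of willingness to use nicotine replacement, watch and app. With 'or', 7 pass. In 3 of those 7 the watch is refused: nicotine replacement and app, nicotine replacement only, and app only. With 'and', 1 of the 8 passes.

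**Later steps that might catch these people.**

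- None of the eight exclusion criteria concerns activity level or the watch.
- The activation assessment (Study Enrollment) is done in the app before randomization. It covers use of app features and the carbon monoxide monitor, so someone refusing the app would probably be found there. That removes one of the 3 watch-refusing combinations (nicotine replacement only) and leaves 2.
- The description of that assessment names no watch check.
- Study Randomization stratifies on self-reported sedentary time, which is not minutes of moderate or vigorous activity and excludes no one.

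**Cost per watch refuser.** With 60 people randomized 1:1, an arm has about 30. Each person without watch data removes about 1/30 = 3.3% of that arm's possible step data. The number of such people is unknown.

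**The case against.** The strongest reply is that the intent is plain. The abstract, Objectives and Overview all speak of insufficiently active people. Staff phone each candidate to confirm eligibility after a web screener that the article does not reproduce, and that screener may already apply the intended rule. Everyone is sent the watch and asked to use it, wear time is itself a feasibility measure, and people with too few valid days are left out of the step analysis. The trial is a feasibility study that states it is not powered for outcome differences.

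Most of this stands, and it limits the seriousness. It does not remove the contradiction: the eligibility rule is stated, and it gives a different answer from the abstract for the same person.

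A reader might go further and infer that already-active entrants would be paid for steps they already take and would shrink the step effect by some definite amount. The documents do not support that.

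- Criterion 5 concerns self-reported aerobic minutes, not steps, and the article gives no conversion between them.
- Step payment begins above 4000 steps a day, which the article gives as roughly the average for Black adults. Anyone walking more than that is paid for existing steps even under a corrected criterion 5. That is a property of the incentive schedule.
- Nothing in the article says what share of entrants would be affected.

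**Conclusion.** The point holds as a fault of wording. Criterion 5 as written admits people who reach the activity level through one intensity, against the abstract and the Overview, which also differ from each other. Criterion 6 as written admits people unwilling to wear the watch that a primary outcome depends on, and no later check for this is described.

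The size cannot be worked out from the documents, neither as a number of people nor as a change in the step outcome. A reader might also infer bias between the arms. That does not follow: entrants are randomized 1:1 and each person's steps are compared with their own pre-quit week, so already-active entrants could at most dilute the step result. No analysis becomes invalid. This is a correction worth making because it is cheap and because eligibility is hard to repair after randomization, but it does not threaten the trial.

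Two assumptions remain: that either activity amount alone meets the cited guideline, and that the screener follows the printed wording, which cannot be checked here.

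**What to change.** 1. State the activity criterion once. Use either below 150 minutes of moderate and below 75 minutes of vigorous activity per week, or, if the cited guideline counts mixed activity, one combined weekly total. Choose one, because they disagree: a person with 100 moderate and 50 vigorous minutes passes the first and, with vigorous minutes counted double, fails the second at 200.
2. Bring the abstract and the Overview into line with that statement.
3. In criterion 6, join nicotine replacement, smartwatch and study app with 'and', so that willingness to use all three is required.
4. Confirm that the web screener and the staff eligibility call apply the same logic. If anyone has already been enrolled, report which rule was used.

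The cost is a short amendment and a check of the screener logic. Some volunteers will no longer qualify, so recruitment may slow slightly against the target of 5 per month.
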